### Strategies to Improve Adherence to the Study Protocol

The participants will be assessed every day during the 7-day treatment period for procedure adherence and placebo capsule consumption. The participants will be asked to return the empty medicine container at the end of the study. Repeated phone reminders to regularly take the medicine from project staff will be given to participants or their family members.

### Intervention Description

This study involves 3 groups, each with specific treatment protocols, shown in Table 1. All 60 eligible participants will be thoroughly informed about the study protocol, and their consent will be obtained. They will be randomly divided into 3 groups: group A, group B, and group C. In group A, participants will receive honey thermal microcautery 2 times (first and seventh days) and placebo capsules for 7 days. Group B will receive standard physiotherapy once a day along with placebo capsules for 7 days. Group C will receive *S cordifolia* oil via 8 drops in each nostril and placebo capsules for 7 days. All baseline parameters will be recorded at the beginning of the trial. This study conforms to the SPIRIT guidelines, ensuring standard execution and ethical handling of the clinical trial. Placebo capsules will be identical in appearance, taste, and administration schedule to mimic a real medication. These will be administered alongside the active intervention twice daily after food, ensuring blinding and consistency throughout the study.

**Table 1. T1:** Grouping and posology.

Group	Intervention	Dose and frequency	Procedure time (min)	Duration (d)	Follow-up
A	Honey thermal microcautery+placebo	2 times a wk	20-30	2 (first and seventh)	On the 8th, 16th, and 32nd days
B	Standard physiotherapy+placebo	Once a day (in the morning)	30-60	7	On the 8th, 16th, and 32nd days
C	*Sida cordifolia* oil via nasal route+placebo	8 drops once a day	20-30	7	On the 8th, 16th, and 32nd days

Study drugs will be stored in a secure location and administered to the participants only under the direction of the investigator. Drug dispensing records will be kept. Any imbalance in the quantities dispensed and returned will be explained.

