## Methods

### Overview

This study is an interventional, randomized, single-blind (assessor), 3–parallel arm study to compare the efficacy of honey thermal microcautery versus standard physiotherapy versus *S cordifolia* oil via nasal administration in the management of FS. We will intervene using honey thermal microcautery 2 times (the first and seventh day) along with placebo capsules twice daily for 7 days. Standard physiotherapy will be administered once a day along with placebo capsules twice daily for 7 days. *S cordifolia* oil via nasal administration will be administered via 8 drops in each nostril along with placebo capsules twice daily for 7 days. Follow-up will be conducted on the 8th, 16th, and 32nd days. Placebo capsules will be administered to reduce the psychological effect that patients might feel from knowing that they are not receiving any oral medicine, especially in the honey thermal microcautery group, where the treatment is administered only 2 times a week.

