### Thermal Microcauterization Procedure

#### Preprocedure (*Poorva Karma*)

The patient will be informed about the procedure, and written consent will be obtained. A pinpointed metallic rod will be made red hot by directly heating it on a fire and smeared with honey [26]. The affected shoulder will be cleaned using a povidone solution, and tender points will be marked.

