#### Main Procedure (*Pradhan Karma*)

The heated rod will be applied to the marked tender points by keeping a 0.5- to 1-cm distance for approximately 1 second at each end. The number of burns will be determined based on the patient’s tolerance and the number of tender points.

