#### Postprocedure (*Paschat Karma*)

Aloe vera pulp will be applied to the treated areas, and *Glycyrrhiza glabra* powder will be sprinkled. The patient will be advised to avoid trauma, exertion, and water on the treated site for at least 12 hours.

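### The placebo capsule cannot blind anyone to arm as the protocol claims, and burns on the measured shoulder could let the assessor recognise group A, most clearly on Day 8

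*Protocol article*

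**What the plan says.** The Methods Overview sets the blinding level: "This study is an interventional, randomized, single-blind (assessor), 3–parallel arm study". The Abstract agrees that only the assessor is blinded.

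The Intervention Description then describes the capsules: "Placebo capsules will be identical in appearance, taste, and administration schedule to mimic a real medication". Its next sentence credits them with a result: "These will be administered alongside the active intervention twice daily after food, ensuring blinding and consistency throughout the study". Table 1 lists placebo alongside the active procedure in every group. The Overview gives the capsules a different purpose: "Placebo capsules will be administered to reduce the psychological effect that patients might feel from knowing that they are not receiving any oral medicine".

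For group A, the cautery preprocedure reads: "The affected shoulder will be cleaned using a povidone solution, and tender points will be marked". The main procedure adds: "The number of burns will be determined based on the patient’s tolerance and the number of tender points". Afterwards: "Aloe vera pulp will be applied to the treated areas, and *Glycyrrhiza glabra* powder will be sprinkled". The timing is given in the Intervention Description: "In group A, participants will receive honey thermal microcautery 2 times (first and seventh days) and placebo capsules for 7 days".

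The range-of-motion section has each movement read three times by goniometer at the glenohumeral joint. Follow-up visits fall on Days 8, 16 and 32. The Sample Size section names shoulder abduction improvement as the primary variable.

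**The concern.** Two things look wrong, and they are linked.

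First, a placebo masks allocation only when some arm gets an active product that looks the same. Here no arm does. The capsule may even out expectations about oral medicine, but it says nothing about the arm and hides nothing. A reader who trusts the sentence would think the comparison better protected than it is.

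Second, the blinding the trial does claim, that of the assessor, is exposed for one arm. Group A's treatment leaves burns on the joint where the outcome is read, and the first follow-up comes one day after the second session. Deciding where end-range lies involves judgement by the person holding the goniometer. The Discussion states the hypothesis that group A will do best, so any expectation effect would probably favour that group. It would act on the variable that sized the trial.

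The VAS, SPADI and McGill scores come from patients who know what they received, so the capsule does not protect those either.

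**Working it through.** The main point rests on setting the sections side by side. The arithmetic only illustrates how much a reading bias could matter.

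**What the capsule can mask**

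| Group | Capsule | Differing treatment | Disguised? |
|---|---|---|---|
| A | placebo | heated rod at tender points of the affected shoulder | no |
| B | placebo | supervised shoulder exercises | no |
| C | placebo | oil drops in the nostrils | no |

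The capsule column is constant, so it carries no information about the group and conceals no difference. The Overview's stated purpose, managing expectation, is consistent with this; the blinding claim is not.

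**What the assessor can see**

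- Site of treatment in group A: the affected shoulder. Site of goniometry: the glenohumeral joint.
- Interval from second session to first follow-up: Day 8 − Day 7 = 1 day.
- Groups B and C: no procedure is described that would mark the shoulder skin.
- Marks would therefore separate A from B and C together, but not B from C.
- Days 16 and 32 are 9 and 25 days after the second session. The article does not say whether marks remain.

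**The plan's own figure**

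Inputs from the Sample Size section: Z values 1.96 and 0.84, SD 0.58, difference 0.526.

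n = 2 × (1.96 + 0.84)² × 0.58² / 0.526² = 2 × 7.84 × 0.3364 / 0.2767 = 19.06, rounded up to 20 per group. This reproduces. The SD is on a graded abduction score; no SD in degrees is given.

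**Illustration of a reading bias**

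Bias is therefore expressed in SD units, with 0, 0.25 and 0.5 SD as assumed values. I simulated the test in Statistical Methods: three normal groups of 20, equal variance, no true effect, and only group A's readings shifted. One-way ANOVA is run at two-sided 0.05 and, if it is significant, Tukey comparisons follow.

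| Bias in group A | False A-versus-one-given-arm difference | False difference of A from either arm |
|---|---|---|
| 0 | about 2% | about 3% |
| 0.25 SD | about 6% | about 9–10% |
| 0.5 SD | about 21% | about 31–32% |

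For orientation on the planning score, 0.25 × 0.58 = 0.145 and 0.5 × 0.58 = 0.29. These are 0.145 / 0.526 = 28% and 0.29 / 0.526 = 55% of the planned difference.

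An unadjusted two-sample t-test with 20 per group would give 12% and 34%, against 5% with no bias. It is not the planned test and should not be used to size this point.

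**The case against.** The strongest reply is that this is a condensed article. Draping or clothing at assessment is operational detail that may sit in the full protocol, and its absence here proves nothing. That stands. The article also does not say that marks are visible, that the shoulder is bare during goniometry, or that the aloe and powder are still present on Day 8. Visibility is an inference from the word burns and the one-day interval. However, a fuller protocol could not rescue the capsule sentence, which is wrong as printed.

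A reader might infer that an independent assessor would necessarily know every patient's arm throughout follow-up. The documents do not support that. Skin marks point to group A only, and their persistence to Days 16 and 32 is unknown.

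A reader might also infer that goniometry is the only outcome assessor blinding could protect. That is too strong: SPADI is administered by the researcher, so an interviewer's knowledge of the arm could matter there too.

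Finally, a cover conceals nothing if the person measuring already knows the allocation. The article has the researcher enrol patients, create the sequence and assign treatment, and names no separate assessor. This objection stands in full, so independence of the person reading the goniometer has to be a condition of the remedy.

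**Conclusion.** The capsule claim is wrong and should be corrected; this needs no assumption beyond the text. The exposure of the assessor is a plausible risk, not a demonstrated failure. It concerns recognition of group A, is strongest on Day 8, and is undocumented at Days 16 and 32. It deserves attention because it bears on the variable that sized the trial and on the arm expected to do best.

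The size of any bias cannot be estimated from the documents. The simulated rates depend on the assumed bias, normality, equal variance and 20 complete patients per group. They show that a moderate reading bias could matter at this sample size, not that one will occur.

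**What to change.** 1. In the Intervention Description, delete the claim that the capsules ensure blinding, keep the expectation-related purpose given in the Overview, and state that patients are not blinded. Reconcile this with the wording on emergency unblinding under Data Collection Plan and Management, which speaks of not revealing the allocation to the participant.
2. For every range-of-motion assessment in all three groups, put the same thin opaque cover over the shoulder before the assessor enters, and ask patients not to mention their treatment.
3. Have the readings taken by existing staff who neither allocated nor treated that patient. Without this condition, step 2 achieves nothing.
4. Report VAS, SPADI and McGill as unblinded patient-reported outcomes, and do not present a difference seen only on them as established superior efficacy.

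The cost is a cloth cover, a few lines of text and some rostering, with no extra visits. If no one other than the researcher is available, step 3 does need a second person. Landmarks are slightly harder to find through a cover, which may add some reading error; that this error is equal across groups is expected but not shown. The article reports 16 of 60 patients recruited by January 2025, so at that date most assessments could still have been covered.

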### Properties of the Drugs Used in *S Cordifolia* Oil

The properties of the *S cordifolia* ingredients are shown in Table 2. The available *S cordifolia* oil of market preparation (*sahastra yoga*) [24] will be used. The treatment group medicine will be procured from good manufacturing practice–certified pharmacies to ensure the product’s safety and quality standards.

**Table 2. T2:** The names of the drugs used to prepare *Sida cordifolia* oil with their Latin names and properties and the parts used.

No.	Ingredient	Botanical name	*Rasa* ^ a ^	*Guna* ^b^	*Virya* ^c^	*Vipaka* ^d^	*Doshaghnata* ^e^	Part used
1	Bala^g^	*S cordifolia*	Madhura^j^	Guru^l^, snigdha^m^, and pichhila^n^	Sheeta^o^	Madhura^j^	Vatapittashamak^s^	Root
2	Tila taila^h^	*Sesamum indicum*	Madhura^j^ and tikta^k^	Guru^l^	Ushna^r^	Ushna^r^	Vatakaphahara^t^	—^f^
3	Godugdha^i^	—	Madhura^j^	Sheet^o^, snigdha^m^, Kinchidkledkarka^p^, and kinchidguru^q^	Sheet^o^	Madhura^j^	Vatpittashamak^s^	—

a Taste.

b Qualities.

c Potency.

d Postdigestive effect.

e Postdigestive action on doshas.

f Not used.

g Country mallow

h Sesame oil

i Cow milk

j Sweet

k Bitter

l Heavy

m Unctuous

n Slimy

o Cold

p Mildly unctuous

q Mildly heavy

r Hot

s Pacifies both Vata and Pitta (bodily humor)

t Removes aggravated Vata and Pitta

### Procedure for Oil Administration Through the Nostrils

Oil administration through the nostrils is conducted in 3 phases [25]: preprocedure (*poorvakarma*), main procedure (*pradhanakarma*), and postprocedure (*aschatkarma*).

#### Preprocedure (*Poorvakarma*)

##### Collection of Material (*Sambar Sangraha*)

The procedure will be conducted in a room free of dust and direct flow of air; with appropriate lighting; and equipped with a table, a chair, medicine for nasal administration, an instrument for administering oil through the nasal route, a towel, cotton, a smoke-producing instrument, a spitting vessel, oil for massage, and material for sudation.

##### Examination of the Patient

Patients unfit for nasal oil administration will be excluded. Informed consent will be obtained, and the patients will be instructed to brush their teeth and clean their mouths.

##### Positioning

The patient will recline comfortably, either sitting with the neck slightly tilted backward or lying on a table with the head supported by a towel. A gentle massage with sesame oil will be applied to the face and head, followed by mild face heating.

### Main Procedure (*Pradhana Karma*)

The patient’s eyes will be covered with a cloth. Eight drops of *S cordifolia* oil will be gradually administered one by one into the distal portion of both nostrils using the index finger of that practitioner’s hand and cotton.

A gentle massage will be administered to the forehead, cheeks, hands, and feet. The patient will be instructed to spit out any excess oil that reaches the mouth. The patient will be kept lying down while watching any symptoms that develop.

### Postprocedure (*Paschatkarma*)

The patient will rinse their mouth with warm water and gargle. Mild medicated *Curcuma longa* smoke will be inhaled to clear the throat. The patient will rest in a warm, wind-free environment; follow a light diet; and drink warm water.

### Thermal Microcauterization Procedure

#### Preprocedure (*Poorva Karma*)

The patient will be informed about the procedure, and written consent will be obtained. A pinpointed metallic rod will be made red hot by directly heating it on a fire and smeared with honey [26]. The affected shoulder will be cleaned using a povidone solution, and tender points will be marked.

#### Main Procedure (*Pradhan Karma*)

The heated rod will be applied to the marked tender points by keeping a 0.5- to 1-cm distance for approximately 1 second at each end. The number of burns will be determined based on the patient’s tolerance and the number of tender points.

#### Postprocedure (*Paschat Karma*)

Aloe vera pulp will be applied to the treated areas, and *Glycyrrhiza glabra* powder will be sprinkled. The patient will be advised to avoid trauma, exertion, and water on the treated site for at least 12 hours.

### Standard Physiotherapy Procedure

#### Preprocedure

The patient will be informed about the exercises, and written consent will be obtained. The patient will be instructed on proper technique and complete preparatory exercises (pendulum swing) [27].

#### Main Procedure

For the shoulder wheel, the patient will stand sideways, align their shoulders with the wheel’s axis, and perform 10 anterior and 10 posterior rotations. Abduction and flexion exercises on a wall-mounted shoulder finger ladder will be conducted next. Patients will stand sideways facing the ladder and perform each movement for 10 repetitions.

#### Postprocedure

The patient will rest for 5 to 10 minutes.

### Outcomes

This study aims to evaluate and compare the efficacy of honey thermal microcautery, standard physiotherapy, and *S cordifolia* oil vial nasal administration using criteria such as the VAS, ROM, the McGill Pain Questionnaire, and the SPADI in patients diagnosed with FS.

#### *Ruja* (Pain; VAS)

The patient will be asked to rate the intensity of the pain they are experiencing on a scale from 0 (no pain) to 10 (worst pain) [28].

There will be 5 pain subcategories: no pain, mild pain, moderate pain, severe pain, and intolerable pain. Numbers from the scale will be used to measure the intensity of the pain, as shown in Table 3. A score of 0 will be considered no pain, a score of 1 to 3 will be considered mild pain, a score of 4 to 6 will be considered moderate pain, a score of 7 to 8 will be considered severe pain, and a score of 9 to 10 will be considered intolerable pain. Identifying patients with FS using this VAS pain assessment will make it easier to include them in this study for treatment.

**Table 3. T3:** The grading on the visual analogue scale (VAS) for frozen shoulder.

Pain level	Pain grade (VAS score)
No pain	0
Mild pain	1 (up to 3)
Moderate pain	2 (4-6)
Severe pain	3 (7-8)
Intolerable pain	4 (9-10)

#### Normal ROM of the Shoulder Joint

The goniometer measures the shoulder’s ROM before and after treatment [29].

Flexion, extension, abduction, adduction, and internal and external rotation are possible shoulder movements, and the normal readings for these movements are shown in Table 4.

**Table 4. T4:** The regular movements and readings for the shoulder joint.

Movement	Normal reading (degrees)
Flexion	180
Extension	50
Abduction	180
Adduction	50
Internal rotation	90
External rotation	90

All the ROM measurements will be taken in a standing position, and the participant will be instructed to place the back of the head, back and buttocks, and heels against the wall to prevent the trunk from moving. Each movement will be measured 3 times on a goniometer at the glenohumeral joint to avoid human error, and the average of 3 readings will be calculated and recorded.

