### Objectives

This study aims to determine the comparative effectiveness of honey thermal microcautery, standard physiotherapy, and *S cordifolia* oil nasal administration in managing FS. The primary objectives are to quantify pain reduction, measured via the visual analogue scale (VAS), and assess improvements in ROM, as well as administer the McGill Pain Questionnaire and Shoulder Pain and Disability Index (SPADI) for each treatment group at specific time points: 8 days, 16 days, and 32 days after the intervention.

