### Secondary Objective

The secondary objective is to evaluate and compare the sustained relief on the 32nd day in each group, defined as maintaining at least a 50% improvement in the VAS score, ROM, McGill Pain Questionnaire score, and SPADI score compared to baseline measurements.

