#### Primary Variable: Abduction Improvement

The primary variable, shoulder abduction improvement, was used to calculate the minimum sample size required for the study, ensuring adequate power to detect a meaningful difference between groups. The primary variable in this study is shoulder abduction improvement, measured as the increase in the range of motion after the intervention. Based on expected differences, variability, significance level, and power, the minimum sample size required was calculated to ensure reliable detection of a meaningful improvement

Where the mean score for abduction in *shudhabala taila nasya* pre=2.23 (as per the study by Revathi et al [22]).

Mom score for abduction in *shudhabala taila nasya* post at follow-up=1.06.

Difference (pretest-posttest)=1.17

SD=0.58.

Considering 45% superiority in the thermal microcautery group=(1.17) × 45 = 0.526

Mean differenсе *δ*=0.526

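### The back-to-wall position set for all range-of-motion readings caps recorded shoulder extension well below the 50 degrees that the protocol lists as normal

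*Protocol article*

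**What the plan says.** The measurement rule is in the Protocol article, Outcomes, under Normal ROM of the Shoulder Joint. It states that "Flexion, extension, abduction, adduction, and internal and external rotation are possible shoulder movements", and Table 4 gives the normal reading for each, with 50 degrees for extension. It then sets one position: "All the ROM measurements will be taken in a standing position", and the participant is told to "place the back of the head, back and buttocks, and heels against the wall to prevent the trunk from moving". It adds that "Each movement will be measured 3 times on a goniometer at the glenohumeral joint" and that the three readings are averaged. No movement is exempted and no second position is described.

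The readings are used in two places. Under Objectives, the primary objectives include to "assess improvements in ROM" at 8, 16 and 32 days. Under Secondary Objective, sustained relief on day 32 means "maintaining at least a 50% improvement in the VAS score, ROM, McGill Pain Questionnaire score, and SPADI score compared to baseline measurements". The sample size section uses one movement only: "The primary variable in this study is shoulder abduction improvement, measured as the increase in the range of motion after the intervention".

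**The concern.** The section fixes one posture for six movements, and for one of them the posture obstructs the movement. Extension takes the arm behind the line of the trunk. With the head, back, buttocks and heels on a wall, the arm reaches the wall after a short arc. From that point the reading reflects where the wall is and not what the joint capsule allows.

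At stake is the validity of one component of a primary-objective measure. The Background section says that frozen shoulder reduces movement in all directions, so extension is relevant to the disease. A participant who gains extension beyond the contact angle would show no gain on the form. Averaging three readings does not help, because it reduces random error and leaves a mechanical stop in place.

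**Working it through.** **1. The plan's own figure, to see whether it is touched.** The inputs are from the sample size sections: SD 0.58, difference 0.526 (45% of 1.17), Z values 1.96 and 0.84.

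n per group = 2 × (1.96 + 0.84)² × 0.58² / 0.526² = 19.06, rounded up to 20.

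This reproduces the stated 20 per group, with power of about 82% at that size. The calculation concerns abduction, which the wall does not block, so the sample size does not depend on this point.

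**2. Where the arm meets the wall.** The document gives no body dimensions, so these are assumptions, shown as a range: shoulder axis 5, 10 or 15 cm in front of the wall; straight arm 60 or 70 cm; with the elbow bent, a 30 cm segment meeting the wall.

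Largest extension angle before contact = arcsin(distance of shoulder axis from wall / length of segment).

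| Axis to wall | 30 cm (elbow bent) | 60 cm (straight) | 70 cm (straight) |
|---|---|---|---|
| 5 cm | 9.6° | 4.8° | 4.1° |
| 10 cm | 19.5° | 9.6° | 8.2° |
| 15 cm | 30.0° | 14.5° | 12.4° |

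Contact therefore comes at about 4 to 15 degrees with a straight arm and about 10 to 30 degrees with a bent elbow. Every case is below the 50 degrees in Table 4.

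**3. What the cap does to the data.** If the contact angle is c, the recorded value is the smaller of the true extension and c.

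- True extension below c is recorded correctly.
- True extension above c is recorded as c. As an illustration, a participant who goes from 20 to 45 degrees with a straight arm has the same recorded value (c, at most about 15) before and after treatment.
- For any two true values, the recorded difference cannot exceed the true difference, and it is zero when both are above c. Real differences between arms in extension are therefore shrunk towards zero.

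**4. The 50% criterion, if it were applied to extension as a proportion of the baseline reading.** A 50% gain can be recorded only if 1.5 × baseline ≤ c, so baseline ≤ c/1.5. For straight-arm contact at 4.1 to 14.5 degrees, baseline must be at most 2.7 to 9.7 degrees. For bent-elbow contact at 9.6 to 30 degrees, it must be at most 6.4 to 20 degrees. Such a gain is out of reach for participants who start above these values, but remains possible below them: going from 5 to 8 degrees is a 60% gain.

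**The case against.** The best defence is that the sentence concerns the trunk. It names the head, back, buttocks and heels, not the arm, and its stated purpose is to stop the trunk moving. Someone standing at a wall edge or against a pillar, with the tested arm free, would satisfy it. Positioning for each movement is also the kind of detail that a condensed article leaves to a fuller protocol or assessor manual.

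This carries limited weight. The article does not leave the position open: it states one for all readings, and a wall edge appears nowhere in the text. A fuller document could cure the problem only by departing from this rule.

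The objections to size do stand. A reader might infer that extension becomes unmeasurable, or reads about zero in every participant at every visit. The geometry does not support that: a small arc remains, the effect is a cap and not a floor, and restriction below the contact angle is still measured correctly. The documents give no baseline extension values, so the share of participants who would reach the cap is unknown.

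A reader might also infer that about 8% of a total range-of-motion score is lost (50 of 180 + 50 + 180 + 50 + 90 + 90 = 640 degrees), or that the sustained-relief rate is forced to 0% in every arm. The first needs a summed score and the second a rule that every movement must improve by 50%; the protocol defines neither. Even under the second, 0% would not follow, as step 4 of the working shows.

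Finally, the posture is the same in all arms, so it does not favour one treatment. The cost is lost sensitivity.

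**Conclusion.** The point holds in limited form. As written, the measurement rule puts the wall in the path of extension and caps recorded extension at about 4 to 15 degrees with a straight arm, or about 10 to 30 degrees with a bent elbow, against a listed normal of 50. Those angles rest on assumed body dimensions and on a wall that continues behind the tested arm. Improvement beyond the contact angle is invisible, and between-arm differences in extension are pulled towards zero.

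The damage is confined to one of six movements. Abduction, the 20 per group, the visual analogue scale, the Shoulder Pain and Disability Index and the McGill questionnaire are untouched. How far the cap reaches into a combined range-of-motion result or the sustained-relief endpoint cannot be stated, because the protocol does not say how the movements are combined. The change is worth making because it is specific and nearly free.

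**What to change.** Keep the back-to-wall position for the other five movements. For extension, specify one standardised position clear of the wall, for example facing it or side-on with the trunk stabilised. Use it at every visit, with the same average of three readings. Alternatively, drop extension from the range-of-motion outcome.

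For participants already enrolled (16 of the planned 60 by January 2025, according to the Results section), either keep the same position within each participant to the last visit, or flag extension readings that were limited by wall contact. Report the flagged readings in a sensitivity analysis. Discarding every extension reading taken against the wall would go too far, since those below the contact angle are valid.

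The cost is one sentence in the measurement procedure, a brief instruction to assessors and a field on the case report form to mark wall contact. The sample size and the main analysis do not change.
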